## Abstract

**Background:**

While spinal cord injury (SCI) caregiving can be a rewarding experience, caregivers often experience reduced mental and physical health.

**Objective:**

This article describes the methodology of a study examining the efficacy of a newly developed telehealth Transition Assistance Program (TAP) for caregivers of individuals with acute SCI.

**Methods:**

A mixed-methods, randomized controlled trial is comparing TAP outcomes to that of a standard-of-care control. The study is recruiting for 48 months and incorporating quantitative outcome measures.

**Results:**

This study was funded by the Craig H. Neilsen Foundation in April 2017. It was approved by the institutional review boards at Virginia Commonwealth University and the Hunter Holmes McGuire Veterans Affairs Medical Center that same year. Participant recruitment and data collection began in 2018.

**Conclusions:**

This study is implementing and testing an SCI caregiver intervention unlike any created before, targeting a critical time period that, until now, other SCI caregiver interventions have overlooked. Research personnel intend to disseminate the intervention and study findings through the publication of manuscripts and presentations at conferences. If the current study shows improvements in caregiver or patient well-being, the TAP for SCI caregivers could become part of the standard of care for acute SCI.

**Trial Registration:**

ClinicalTrials.gov NCT03244098; https://www.clinicaltrials.gov/ct2/show/NCT03244098

**International Registered Report Identifier (IRRID):**

DERR1-10.2196/28256

## Introduction

Each year in the United States, 18,000 individuals experience a new spinal cord injury (SCI), and nearly 294,000 are living with SCI [1]. Individuals with SCI experience myriad medical complications [2] and reduced mental health [3,4], which bears on their own health-related quality of life (HRQoL) [5]. Although only one family member typically experiences an SCI, the injury affects the entire family [2,6]. Many family caregivers experience strain, depression, anxiety, lower general health [7,8], and burden [9-11].

Unfortunately, SCI caregivers perceive inadequate support from their social network, profound isolation, and insecurity in the weeks after hospital discharge [12,13]. The first few months are particularly stressful as caregivers cope with unstable social support and even their own wavering health [14]. Substantial research has been conducted on caregivers of individuals with various disabilities [15], but considerably less has focused on SCI caregivers. The current review uncovered several SCI caregiver interventions with empirical support; however, studies either did not target the specific acute discharge time period in the current study or psychosocial outcomes. Rodgers et al [16] developed the SCI Multiple-Family Group Treatment and targeted families who had been coping with SCI for 6 years on average. Schulz et al [11] compared the effectiveness of a caregiver-only intervention against an intervention for SCI caregiver-recipient dyads, but the individuals with SCI had sustained the SCI on average 7.7-9 years prior. Kurylo et al [17] developed the FOCUS program, which was incorporated by Elliott and Berry [18] into a formalized Problem-Solving Training program; however, no caregiver in either study participated during the first month after discharge. Molazem et al [19] showed positive results for a psychoeducational intervention on SCI caregiver HRQoL; however, the average length of time as a caregiver was 9 years. Hearn et al [20] showed that a web-based mindfulness intervention was helpful in reducing SCI caregiver anxiety and depression; however, the minimum length of time since injury was 1 year. Finally, Juguera Rodríguez et al [21] showed that simulation training for SCI caregivers during inpatient rehabilitation can improve competency in caregiver-related tasks but did not target psychosocial outcomes.

To improve SCI rehabilitation through stronger informal caregiving, this study is developing and evaluating a telehealth Transition Assistance Program (TAP) for caregivers of individuals with SCI during the transition from acute rehabilitation to home. This is the first SCI caregiver intervention to occur during this critical time and to target a host of important caregiving psychosocial variables. The TAP was previously developed for stroke caregivers [22] and is being modified for SCI and implemented at 2 state-of-the-art SCI rehabilitation facilities.

## Methods

### Study Design

This study is a prospective, mixed-method, randomized controlled trial incorporating a before-and-after design with a standard-of-care control wherein caregivers receive no formalized, structured postdischarge support. The study is recruiting over a period of 48 months.

### Setting

The TAP program is delivered via telehealth at a Veterans Affairs (VA) medical center and an academic medical center in the same urban area.

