### Randomization

A randomization schedule was created with a web-based, computerized random number generator. We maintain allocation concealment and eliminate possible selection or recruitment biases by keeping the randomization schedule concealed from on-site staff engaged in recruiting. A randomization schedule was generated by the PI who does not have any contact with participants, and a sealed envelope with the sequentially numbered randomization schedule was prepared prior to recruitment of any participants. After a project coordinator determines eligibility for a prospective dyad and obtains informed consent, the PI is notified and then opens the sealed envelope. The group assignment based on the predetermined sequence for that participant to 1 of the 2 groups is revealed at that point. If the participant is in the TAP group, an interventionist is then assigned to that participant. In order to control bias and preconceptions in collecting data, the interventionist does not collect baseline or follow-up data from participants with whom they intervene.

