#### Sessions 2-5

The interventionist administers four 1-hour telehealth clinic-to-home sessions with the SCI caregiver at 1, 2, 4, and 6 weeks after hospital discharge. One of the rehabilitation centers already had in place secure and encrypted telehealth technology that allows an interventionist on-site to meet virtually with a caregiver at home via personal computers or mobile devices. For caregivers who do not have a personal computer, mobile device, or adequate internet connection, a telephone-based approach is used. The individual with SCI may or may not be in the same room as the caregiver during these sessions, depending on the wishes of the caregiver. These sessions involve the same general format. The interventionist brings his or her notes from the previous sessions and from the rehabilitation team’s input. The interventionist reviews the content of these notes with the caregiver, checking in to see whether the problems are still present and to what extent. The interventionist engages in supportive problem solving and refers the caregiver to the guidebook sections relevant to the issues, walking the caregiver through those sections. Because of this format, the TAP is specifically designed for interventionists to tailor its use in future studies or administrations not only according to possible facility differences in what may be necessary for the intervention but also for differences in caregiver responsibilities and needs within a single facility. The entire structure of the TAP is centered around the caregiver’s most pressing needs. The interventionist takes notes on the continued problems and strategies for resolving them.

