### Data Analysis

A Greenhouse-Geisser–adjusted RMANOVA with 1 fixed effect of treatment condition (TAP vs control), the repeated measures over time (baseline and 2 and 4 months after discharge), and the treatment condition by time interaction will be conducted for the set of dependent variables. If an omnibus effect is found, follow-up Holm-Bonferroni–corrected ANOVAs will identify specific locations of effects. Our research has shown that these dependent variables rarely correlate with each other higher than .60 in SCI caregivers [5] so do not reach the .70 level that is often identified as problematic in RMANOVA [33].

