Given the study’s presence at both a VA medical center and an urban academic medical center, any study findings should have high generalizability to both the general population and veterans with SCI. Our TAP for SCI caregivers is innovative in that it fills one of the biggest gaps in SCI rehabilitation by aiming to improve the mental health of and quality of informal care provided by caregivers immediately as they transition into their caregiving role. The study’s telehealth format surmounts geographical barriers and links SCI caregivers via telehealth technology to the specialized center from which the individual with SCI received acute rehabilitation, thereby overcoming the discontinuity in care that all too often affects individuals with SCI and their family after discharge. If shown in the proposed study to improve caregiver mental health, informal care, and SCI rehabilitation, the TAP for SCI caregivers could be exported and evaluated much more widely across other rehabilitation facilities in the United States and hopefully become part of the standard of care for SCI.

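### Site is missing from the stated analysis model of a 44-dyad trial at two unlike centers; adding site and site-by-time costs little and protects the estimate if change over time differs by site

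*Protocol article*

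**What the plan says.** All places are in the protocol article.

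- **Setting:** two centers of different type take part. "The TAP program is delivered via telehealth at a Veterans Affairs (VA) medical center and an academic medical center in the same urban area".
- **Randomization:** one list in one sequence is described. "a sealed envelope with the sequentially numbered randomization schedule was prepared prior to recruitment of any participants". No site list or stratum is mentioned.
- **Data Analysis:** the model is enumerated, "with 1 fixed effect of treatment condition (TAP vs control), the repeated measures over time (baseline and 2 and 4 months after discharge". The only further term listed is the interaction of these two. Site does not appear.
- **Study Design:** one control description covers both centers, "a standard-of-care control wherein caregivers receive no formalized, structured postdischarge support".
- **Sessions 2-5:** "One of the rehabilitation centers already had in place secure and encrypted telehealth technology". Under Session 1, the interventionist prepares with the rehabilitation team of the facility concerned.
- **Discussion:** the two centers are taken to stand for two populations, "any study findings should have high generalizability to both the general population and veterans with SCI".
- **Participants, Recruitment, and Sample Size:** 44 dyads, 22 per arm, at Cohen f = .25 and 80% power. The expected number of dyads per center is not given.

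**The concern.** A VA center and an academic center are an obvious source of variation between dyads, and the article itself treats them as serving different populations. Yet neither the described allocation nor the stated model holds site constant. The model matters more, because it is written out term by term and site is not among the terms.

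Two things are at stake. First, if caregivers or patients at the two centers change differently between baseline and 4 months, and the arms happen to differ in site mix, part of that site difference ends up in the TAP-control difference. A single trial of 44 dyads gets one draw of the randomization, so the average over many draws is little comfort if this draw is uneven. Second, even with balanced arms, site differences in change add to the error against which treatment by time is tested, and a trial of this size has little precision to spare.

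**Working it through.** **Inputs from the article:** 44 dyads, 22:22, three time points including baseline, f = .25, power 80%.

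**Assumptions:** the site split; the size of any site difference in change; alpha 0.05; within-dyad correlation 0.5. I take treatment by time as the efficacy comparison, because baseline is one of the repeated measures. The simulations treat one outcome at a time.

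**1. The plan's own figure.** For the interaction, λ = f²·N·m·ε/(1−ρ), with df (m−1)ε and (N−2)(m−1)ε. At ρ = 0.5 and ε = 0.5, λ = 0.0625 × 44 × 3 × 0.5/0.5 = 8.25 on 1 and 42 df, giving power 0.801. So 44 can be reproduced, although the article does not state these settings. The figure does not decide the site question.

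**2. Chance of a site imbalance.** With k dyads from the smaller center and x of them in the TAP arm, x is hypergeometric (44, k, 22). The difference in site share is |x − (k − x)|/22 = |2x − k|/22.

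| k (assumed) | P(difference ≥ 20 points) | smallest attainable difference ≥ 20 points |
|---|---|---|
| 11 | 0.162 | 5/22 = 22.7 points |
| 15 | 0.203 | 5/22 = 22.7 points |
| 22 | 0.131 | 6/22 = 27.3 points |

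The probabilities do not move steadily with k because only every second multiple of 1/22 is attainable.

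**3. What an imbalance does.** Treatment by time uses contrasts over time whose weights sum to zero. A site difference that is the same at all three visits drops out. A site difference in change does not:

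bias = imbalance in site share × site difference in change

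Examples: 0.2 × 0.5 SD = 0.10 SD; 0.2 × 1 SD = 0.20 SD.

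**4. Type I error without a site term** (44 dyads, 6,000 simulated trials per setting, site shares 50:50 and 70:30).

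- Over all draws: 0.047 to 0.056 in every null setting.
- Among draws with an imbalance of 20 points or more: about 0.05 if sites differ only in level (0.5 SD); 0.06 to 0.07 if change differs by 0.5 SD; 0.10 to 0.14 if it differs by 1 SD.
- With site and site-by-time in the model, that last range falls to 0.05 to 0.06.

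**5. Power with and without site.** Contrast of mean follow-up minus baseline, assumed TAP effect 0.6 SD, sites 29:15:

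| Site difference in change | without site | with site |
|---|---|---|
| none | 0.62 | 0.61 |
| 0.5 SD | 0.59 | 0.61 |
| 1 SD | 0.50 | 0.60 |

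The full treatment-by-time F test shows the same pattern: 0.518 against 0.513 with no site effect (50:50), and 0.43 to 0.44 against 0.49 to 0.50 if change differs by 1 SD.

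**6. Which site term.** A site main effect explains variation in a dyad's average over the three visits. The treatment-by-time test uses within-dyad differences, so with complete data that term leaves it unchanged. Only site by time absorbs a site difference in change.

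**7. Degrees of freedom.** Between dyads: 44 − 2 = 42 becomes 41. Within dyads: 2 × 42 = 84 becomes 82.

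**The case against.** The strongest reply is that randomization already takes care of this. Overall type I error is near 5% without any site term, level differences cancel, and at a 0.5 SD site difference in change the error rate rises only to 0.06 to 0.07 even in unbalanced draws. All of that stands. A reader might infer that a site imbalance would be mistaken for a TAP effect; the calculations do not support so general a claim.

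Three further inferences are tempting and should not be made.

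- *Standard care differs between the centers.* The article does not say so; Study Design gives one control description for both.
- *Uneven telehealth infrastructure creates a false effect.* The article does not say that the second center lacked telehealth during the trial. The telephone fallback depends on the caregiver's equipment, and the guidebook and fidelity checks are common to the study. A difference in delivery would in any case touch only the TAP arm. It could make the effect vary by center, but could not produce an effect where there is none.
- *Randomization was not stratified.* The article mentions no strata, but it is a condensed account and the full protocol may describe them. Nor is there a good case for re-blocking the remaining allocation: 31 dyads had enrolled by March 2021 (Results), leaving at most 44 − 31 = 13.

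It is also fair to say that the size rests on assumed figures. The 0.10 SD is one fifth of the planned effect if f = .25 is a between-group effect (d = 2 × .25 = 0.50). If f is the interaction, with equal baselines and a constant follow-up difference d, then f = d/√18, d is about 1.06, and 0.10 SD is under a tenth of it.

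The reply does not dispose of the missing model term. Data Analysis specifies the model in full, so this is more than detail left out of an article.

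**Conclusion.** The point holds in limited form. The stated model leaves out the one design feature that visibly separates the dyads into two groups. Test validity averaged over randomizations is not threatened. What is exposed is the estimate in the trial as realized, and its precision, and only if change over time differs by center.

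Under assumed site splits there is about a 13% to 20% chance of an imbalance of 20 points or more. The resulting shift is 0.10 SD if change differs by 0.5 SD between centers. Without site, power in the contrast simulation is about 2 points lower at that difference and about 10 points lower at 1 SD, which is a strong assumption. The site split, the site difference in change, alpha, the correlation and the 0.6 SD effect are all assumptions; the article gives none of them. The change is worth making because it costs so little, not because a bias has been shown.

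**What to change.** Before unblinded analysis, amend the Data Analysis model to include site (VA or academic) and site by time alongside treatment, time and treatment by time, and carry both terms into the follow-up ANOVAs. Adding site without its time interaction would not serve the purpose.

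Optionally, report the TAP-control difference by center descriptively, without a test. That would also let readers judge the Discussion's generalizability statement against what was seen at each center.

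The cost is one between-dyad and two within-dyad degrees of freedom, and about 1 point of power or less if site turns out not to matter. Which center each dyad came from is already known, so no new data are needed, and the allocation procedure need not change.

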### Caregiver Guidebook Development

The research team developed a guidebook entitled “A Guidebook for SCI Caregivers” based heavily on research examining the needs of SCI caregivers, as well as on other published studies on SCI. Research has shown that the top reported needs of SCI caregivers include information, economic support, emotional support, community support, and respite needs [23]. This guidebook was created to target these needs directly and therefore includes chapters addressing (1) basic medical information about SCI; (2) common caregiver experiences; (3) SCI recovery issues such as disability, disruption in sense of self, social isolation, and depression; and (4) resources to assist SCI caregivers. An extensive formative evaluation of the guidebook was conducted including focus groups with SCI clinicians at the rehabilitation facilities at the VA and academic medical centers. The guidebook was piloted with SCI clinicians and caregivers who provided quantitative and qualitative feedback on the guidebook’s appropriateness.

### Participants, Recruitment, and Sample Size

The eligibility criteria for individuals with SCI and caregivers are the following: (1) between the ages of 18 and 89 years; (2) able to verbally communicate in English; (3) access to a computer, telephone, or other device capable of telecommunication; (4) no other serious mental or neurological disorders; (5) no active serious substance use disorder; and (6) being a dyad composed of 1 individual with a new diagnosis of SCI or significant new loss of function related to an old SCI and 1 individual identifying as a new informal caregiver. All individuals with SCI are those participating in a comprehensive residential rehabilitation program.

A power analysis was performed using G*Power 3.1. An estimated medium effect size of Cohen *f*=.25 was used to determine the sample size needed for a repeated-measures multivariate analysis of variance (RMANOVA) with 3 time points and 2 groups. With 80% power (1 - β), a sample size of 44 dyads is needed in order to detect the hypothesized medium-sized effects on the various outcomes. We selected a 48-month enrollment period because, based on SCI admissions data and previous studies conducted at the 2 rehabilitation sites, this window is necessary to enroll 44 patient-caregiver dyads (n=88), of which 22 dyads will be in the treatment group and 22 will be in the control group. This RMANOVA would uncover all large and medium-sized effects, but no small-sized effects.

Recruitment is conducted on site and in-person by either the research coordinator or the site’s principal investigator (PI). Patient-caregiver dyads are randomly assigned to the TAP treatment or control group, and each individual with SCI and caregiver is paid US $20 per data collection for a total of US $60 each.

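### The 80% power for medium effects is worked out for one outcome and does not carry over to the planned omnibus test and Holm-corrected follow-ups; the claim to uncover every medium effect is wrong

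*Protocol article*

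**What the plan says.** Participants, Recruitment, and Sample Size: "A power analysis was performed using G*Power 3.1". The design entered is a "repeated-measures multivariate analysis of variance (RMANOVA) with 3 time points and 2 groups", and the effect size is Cohen f = .25, labelled medium. The conclusion drawn for 80% power is that "a sample size of 44 dyads is needed in order to detect the hypothesized medium-sized effects on the various outcomes". The arms are equal: "22 dyads will be in the treatment group and 22 will be in the control group". The paragraph's closing claim is "This RMANOVA would uncover all large and medium-sized effects, but no small-sized effects".

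Data Analysis: a Greenhouse-Geisser-adjusted RMANOVA with treatment, time and their interaction "will be conducted for the set of dependent variables". If the omnibus test is significant, Holm-Bonferroni-corrected ANOVAs follow. The section adds that these variables rarely correlate above .60 in SCI caregivers.

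Data Collection 1 lists seven constructs in the caregiver packet.

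**The concern.** The power inputs contain nothing for the number of outcomes or for the Holm step, yet the 80% is claimed for the various outcomes and the closing sentence promises that no medium or large effect will be missed. With 22 dyads per arm, a reader who takes that sentence at face value would treat a null result as excluding medium and large effects. The Discussion ties possible adoption into standard care to the results, so how a null result is read matters.

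Two things make this worse. A medium f on a treatment-by-time interaction is a much larger arm difference than most readers would take medium to mean. And the test is called multivariate while carrying a correction that belongs to the univariate repeated-measures F, so it is unclear which test the 80% describes.

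**Working it through.** **Inputs from the article.** f = .25, 80% power, 2 groups, 3 time points, N = 44 (22 + 22), seven caregiver constructs, correlation between outcomes rarely above .60.

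**Assumed, because the article does not give them.** Two-group F test at alpha .05; within-person correlation ρ of .2 to .7; nonsphericity ε from .5 (the lower bound for 3 time points) to 1; inter-outcome correlation r of .3 to .6.

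**1. The article's figure, one outcome.** Univariate treatment-by-time test: λ = f²·N·3·ε/(1−ρ), with df 2ε and 2(N−2)ε.
- ρ = .5, ε = .5: λ = .0625 × 44 × 3 × .5/.5 = 8.25, df 1 and 42, power 80.1%. Smallest even N for 80%: 44.
- ρ = .2, ε = 1: λ = 8.25/.8 = 10.31, df 2 and 84, power 81.3%. Smallest even N: 44.
- ρ = .5, ε = 1: λ = 16.5, power 95.6%. Smallest even N: 28.

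So 44 reproduces for one outcome at unadjusted alpha.

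**2. Holm step over seven outcomes.** The first threshold is .05/7 = .0071. Power for f = .25 on a given outcome at N = 44:
- ρ = .5, ε = .5: 52% (72 dyads for 80%).
- ρ = .2, ε = 1: 55% (66 dyads for 80%).
- ρ = .5, ε = 1: 83% (42 dyads for 80%).

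The first step is the relevant threshold when no other outcome has been rejected; it relaxes as others are. Passing the omnibus test first can only lower these figures. Counting only the six caregiver instruments described under Outcome Measures changes the first two to 55% and 57%.

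**3. Omnibus test on seven scores, f = .25 on each, sphericity over time.** Two time contrasts per score give 2p = 14 dimensions. λ = [f²·N·3/(1−ρ)]·p/(1+(p−1)r), with df 14 and 44−2−14+1 = 29.

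| ρ | r | λ | power |
|---|---|---|---|
| .2 | .3 | 10.31 × 7/2.8 = 25.8 | 79% |
| .2 | .6 | 10.31 × 7/4.6 = 15.7 | 52% |
| .5 | .3 | 16.5 × 7/2.8 = 41.3 | 96% |
| .5 | .6 | 16.5 × 7/4.6 = 25.1 | 78% |

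**4. The closing sentence.** At 80% power each medium effect is missed with probability 20%. Seven independent ones would all be found with probability 0.8⁷ = 21%. Nor are small effects ruled out: single-outcome power at f = .10 is 20% (ρ = .5, ε = .5) to 28% (ρ = .5, ε = 1).

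**5. What f = .25 means between arms.** Take no arm difference at baseline and d SD at both follow-ups. The arm-difference profile (0, d, d) has mean 2d/3. Halving its deviations gives interaction terms of size d/3, d/6 and d/6 in each arm. Their mean square is (1/9 + 1/36 + 1/36)d²/3 = d²/18, so f = d/√18 = 0.2357d.
- f = .25 gives d = .25 × √18 = 1.06 SD.
- d = 0.5 gives f = .118. Single-outcome power at N = 44 with ε = 1: 25% (ρ = .2), 28% (.3), 37% (.5), 58% (.7). With ρ = .5 and ε = .5: 26%.
- Difference detectable with 80% power, one outcome, no Holm step, solving the step 1 formula for d: 0.83 SD (ρ = .5) to 0.98 SD (ρ = .3) with ε = 1; 1.06 to 1.25 SD with ε = .5.

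**The case against.** The strongest defence is that the calculation is sound on its own terms. The article defines medium as Cohen f = .25, which is the usual label for that index, and 44 follows from ordinary G*Power settings. At ρ = .5 with sphericity, 44 dyads also give 78-96% for the seven-score omnibus and 83% at the first Holm step. It is even possible that 44 came from ρ = .5, ε = 1 and alpha .05/8, which also returns 44. Alpha, ρ, ε and the exact set of outcomes may stand in a fuller protocol or analysis plan, and leaving them out of an article is not a fault.

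Most of this stands, and it rules out several stronger readings:
- A reader might infer that 44 is an arithmetic error. Step 1 shows that it is not.
- A reader might infer that the multivariate test needs 158 dyads and has 28% power at 44. That holds only if f = .25 is read as the multivariate index f(V), whereas the article says Cohen f. With Cohen f, the multivariate interaction test on one outcome gives 80% at ρ = .2 and 95% at ρ = .5.
- A reader might put all caregiver and patient scores, or every subscale, into one model and find very low power or a test that cannot be computed. The article does not say that they enter one model, and its correlation argument is about caregivers.
- A reader might say that power for 0.5 SD is always well below 50%. At ρ = .7 with sphericity it is 58%.

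The defence does not rescue the text. The sample-size paragraph mentions no adjustment for several outcomes, so its 80% cannot be read as covering them. Whatever settings were used, the closing sentence is untrue, and the arm-difference conversion in step 5 is unaffected.

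**Conclusion.** The point holds in a limited form. The stated 80% is a single-outcome figure, and it is claimed for an analysis of a set of outcomes where it is not shown to apply. If 44 came from a single-outcome treatment-by-time calculation at alpha .05, power for a medium effect on a given outcome is about 52-55% at the first of seven Holm steps. Omnibus power is 52-79% at ρ = .2, or 78-96% at ρ = .5 with sphericity. The shortfall therefore depends on unstated inputs, and it would be wrong to say flatly that the planned analysis cannot reach 80%.

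Two parts do not depend on how 44 was obtained. The closing sentence is false at the power that the article itself states. And f = .25 on this interaction is about 1.06 SD at both follow-ups, so a null result would not exclude a 0.5 SD difference, for which single-outcome power is about 25-37% at ρ of .2 to .5. That conversion assumes equal arms at baseline and the same difference at 2 and 4 months; if the difference grows linearly from baseline, f = .25 corresponds to 1.22 SD at 4 months.

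**What to change.** Keep 44 dyads and change the wording:
1. Delete the sentence claiming that all medium and large effects, and no small ones, would be uncovered.
2. State that 80% power at f = .25 applies to one outcome at unadjusted alpha, and give the alpha, ρ and ε actually entered in G*Power. If a divided alpha was entered, say so; the Holm shortfall must then be recomputed.
3. Name the test to which the figure refers: the multivariate omnibus test or the Greenhouse-Geisser-adjusted univariate F.
4. Give the power of the omnibus test and of the Holm-corrected ANOVAs for the set of outcomes that will be analysed.
5. Express the detectable effect as an arm difference. For one outcome without the Holm step this is about 0.83-0.98 SD with sphericity and ρ of .5 to .3, or about 1.06-1.25 SD at ε = .5. Replace these ranges with the value for the settings used.
6. State that a null result does not exclude a medium difference between arms.

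The cost is retrieving the G*Power settings and rewriting one paragraph. No participants are added and the analysis need not change. The downside is that the stated sensitivity becomes less favourable.
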